### Sample size

Sixty participants (*n* = 60) will be recruited after the run-in period and allocated to the RG group (*n* = 30) and the placebo group (*n* = 30). The sample size was calculated considering the expected change of glycosylated hemoglobin (HbA1c) (primary outcome) of the participants by software PASS15.0. Previous studies have reported that formula including Coptis root and ginseng had statistically and clinically significant reduction of absolute HbA1c by about 0.72% [34, 35] and mean change in HbA1c by about 0.70% [36]. The sample size was calculated to have 80% power to detect a moderate 0.65-SD difference in HbA1c, with an alpha/*α* value of 0.05. Additional participants will be recruited until the required number is achieved (*n* = 30) per group to account for the estimated drop-out rate of 15%. Therefore, we take the sample size as 30 in both groups.

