## Methods

### Study design

This protocol is designed as a randomized and placebo-controlled trial. Participants and investigators are blinded. A total of 60 subjects will be recruited at the Section II of Endocrinology & Nephropathy department of Dongzhimen Hospital affiliated to Beijing University of Chinese Medicine. They will be randomized in a 1:1 ratio to an experiment group (RG formula) and a control group (placebo). Patients in both groups are given basic blood glucose control. Only the use of insulin and insulin secretion promoters (such as thiazolidinedione and sulfonylurea) can be allowed as basic control in both groups, as current research has shown no significant influence on gut microbiota in neither drugs. The trial flow diagram is illustrated in Fig. 1. The SPIRIT Checklist is shown in Supplemental file 1 [26].

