#### Primary outcomes

The primary outcome in this study is glycosylated hemoglobin (HbA1c), which means the comparison of HbA1c change between two groups after 12 weeks of intervention. HbA1c is a critical indicator for the diagnosis of T2DM, which can reflect average levels of glycemia during the preceding 3 months and is widely used for diabetic complication assessment [28]. It is considered the gold standard for predicting glycemia-associated risks for the microvascular and macrovascular complications of diabetes mellitus over 5–10 years [29]. Therefore, the value of HbA1c in the care of patients with T1DM and T2DM is unassailable [30]. Professional societies, public health organizations, regulatory agencies, patients, and clinicians have focused on HbA1c levels to gauge the quality of diabetes care, and over time, HbA1c level has supplanted other indicators of the quality of diabetes care, such as blood glucose levels and symptoms of hyperglycemia, despite being a surrogate rather than a direct marker of glycemic control [31]. In addition, careful regulation of blood glucose concentrations in patients with diabetes mellitus normalized HbA1c over 6 weeks [32], so it has also excellent reliability and validity and is sensitive enough for clinical and research practice.

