### Statistical analysis

SPSS 20.0 software was used for the statistical analysis of data. Measurement data were described as mean (M) ± standard deviation (SD). Normality of continuous data was evaluated using the Kolmogorov–Smirnov test and Q–Q plot. If the paired samples were in accordance with normal distribution, the *t*-test of the paired samples was used for pairwise comparison. If not, the nonparametric test was adopted. If the two independent samples were in accordance with the normal distribution and homogeneity test of variances, the *t*-test of the independent sample was used. The *t*'-test was used when the variance was not in uniform and the nonparametric test was adopted when the samples were not in accordance with normal distribution. The covariance analysis will be performed regardless of the comparability in the baseline of Hba1c values of the two groups before treatment. Enumeration data like gender and medical history was described statistically by frequency. The chi-square test and Wilcoxon rank sum test were used to determine whether there was comparability between the two groups. All statistical tests are bilateral, and a *P* value ≤ 0.05 would be considered statistically significant.

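### Thirty per arm does not reproduce the stated 80% power for a 0.65-SD HbA1c difference under two-sided 5% testing: an unadjusted t-test has about 70%, and about 62% if a 15% loss is not replaced

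*Protocol article*

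**What the plan says.** All references are to the protocol article.

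- **Sample size:** the section states: "The sample size was calculated to have 80% power to detect a moderate 0.65-SD difference in HbA1c", at alpha 0.05, computed in PASS. Sidedness, the test and any baseline correlation are not given. Earlier studies' HbA1c reductions of about 0.72% and 0.70% are mentioned, but no SD is.
- **Sample size, drop-out:** the text continues "value of 0.05. Additional participants will be recruited until the required number is achieved", with that number given as 30, "per group to account for the estimated drop-out rate of 15" per cent. It closes: "Therefore, we take the sample size as 30 in both groups".
- **Primary outcomes:** the primary endpoint is "the comparison of HbA1c change between two groups after 12 weeks of intervention", so it is a between-group comparison.
- **Statistical analysis:** "All statistical tests are bilateral", with significance at P of 0.05 or less. Independent-sample t-tests (or the unequal-variance or nonparametric version) are listed. A covariance analysis is also to be done whatever the baseline HbA1c balance.
- **Study design, Study setting and Allocation concealment mechanism:** 60 patients, 1:1, and a list of exactly sixty numbers, 1 to 30 for the experimental group and 31 to 60 for control.

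**The concern.** The section gives a standardised effect, a power, an alpha and a sample size. The missing SD therefore does not prevent a check, and no outside figure is needed. Two things look wrong. First, 30 per arm is too few for a two-sided 5% comparison of 0.65 SD. Second, the same 30 serves both as the required number and as the number that allows for 15% drop-out, so no inflation is visible.

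The stated power is the figure a reader would use to interpret a non-significant HbA1c result. If it holds only for a test the plan does not use, or under an assumption it does not state, the trial's sensitivity to its own target effect is presented too favourably.

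**Working it through.** **Inputs.** Standardised difference d = 0.65, power 80%, alpha 0.05, 30 per arm and drop-out 15% (Sample size); 1:1 allocation (Study design); two-sided testing (Statistical analysis). The 0.65 SD is taken to be in units of the SD of the variable tested.

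**Step 1. Where 30 comes from.** Normal approximation: n per arm = 2(z_alpha + z_beta)²/d².

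- One-sided 5%: 2(1.6449 + 0.8416)²/0.4225 = 29.27, so 30. The noncentral t gives 29.97, so 30, with 80.0% power.
- Two-sided 5%: 2(1.9600 + 0.8416)²/0.4225 = 37.15, so 38. The noncentral t gives 38.14, so 39.
- Paired (one-sample) test, two-sided: 20.58, so 21. This does not match.

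Of the standard variants tried, only the one-sided calculation without drop-out returns 30.

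**Step 2. Drop-out.** Two-sided: 39/0.85 = 45.9, so 46 per arm (92 in total). Even one-sided: 30/0.85 = 35.3, so 36 per arm. Conversely, 30 × 0.85 = 25.5 per arm, or 51 in total.

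**Step 3. Power of the unadjusted two-sided t-test.** Noncentrality = d√(n/2), with 2n − 2 degrees of freedom.

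| Evaluable per arm | Noncentrality | Critical t | Power | Detectable difference at 80% |
|---|---|---|---|---|
| 30 | 0.65√15 = 2.517 | 2.002 | 69.7% | 0.736 SD |
| 25.5 | 0.65√12.75 = 2.321 | 2.010 | 62.4% | 0.800 SD |

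One-sided, 25.5 per arm would give 74.0%.

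**Step 4. Covariance analysis.** Let r be the baseline/week-12 correlation and σ the SD of HbA1c, equal at both times. The adjusted residual SD is σ√(1 − r²), and the SD of change is σ√(2(1 − r)). The effective standardised difference is therefore:

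- 0.65/√(1 − r²) if 0.65 SD refers to HbA1c itself (raw SD);
- 0.65√(2/(1 + r)) if it refers to the change.

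Reaching 80% with 30 per arm needs an effective difference of 0.736:

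- raw SD: r ≥ √(1 − (0.65/0.736)²), about 0.47;
- SD of change: r ≤ 2(0.65/0.736)² − 1, about 0.56.

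With 25.5 per arm the required value is 0.800, and the limits become r of at least about 0.58 (raw SD) or at most about 0.32 (SD of change).

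At r = 0.5 both readings give 0.65/√0.75 = 0.751. Power is then about 82% with 30 per arm and about 75% with 25.5. At r = 0.7 the two readings diverge: 77% (change) to 93% (raw) with 30 per arm, and 69% to 89% with 25.5. The extra degree of freedom used by the covariate changes these by less than 0.1 percentage point.

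**The case against.** **The covariance analysis.** The strongest defence is that the plan commits to an analysis adjusted for baseline HbA1c, and step 4 shows that it can reach 80% with 30 per arm at quite ordinary correlations. A reader might infer from the t-test figures that the 80% claim is false for every planned analysis, or that the trial has a 30% to 38% chance of missing a 0.65-SD effect whatever is done. The documents do not support that. Those miss rates belong to the unadjusted test; at r = 0.5 the adjusted analysis misses about 18% to 25%. What remains is that the Sample size section states no correlation, does not mention adjustment and does not say which SD it means. The adjusted analysis could make 80% attainable, but nothing in the section shows that it was the basis of the calculation.

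**Replacement of drop-outs.** The sentence about recruiting additional participants can be read as replacing losses until 30 per arm complete. Only the 70% figure would then apply. The fixed total of 60 and the list of exactly sixty numbers, with no spares, favour the reading without replacement, but they do not settle it. The 62% is therefore conditional.

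**HbA1c units.** It is tempting to divide the quoted 0.70% by 0.65 to obtain an SD and express the shortfall in HbA1c points. The section never ties that reduction, or the 0.72% beside it, to the 0.65-SD target, so the conversion has no basis.

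**A fuller document.** A full protocol or SAP may explain more. The point is not an omission, however: the power, alpha, sidedness, effect and sample size printed in the article do not agree for a plain two-group comparison.

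**Conclusion.** The point holds as a failure to reproduce. Under the plan's own two-sided 5% testing, 80% power for 0.65 SD needs 39 evaluable per arm, against 30 planned. For the unadjusted t-test, type II error is about 30% with 30 evaluable per arm and about 38% if 15% are lost and not replaced, against the 20% stated. These figures assume that 0.65 SD is in units of the variable tested.

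The match with a one-sided calculation is close, but it is an inference about origin; the article does not say that a one-sided test was used. Whether the covariance analysis has 80% power cannot be decided from the article, because the answer depends on an unstated correlation and on which SD is meant. The finding concerns the stated power only; it implies no bias and no inflation of type I error.

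**What to change.** Keep 60 randomised and rewrite the Sample size paragraph to:

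1. State two-sided alpha 0.05 and name the test.
2. Give the t-test power for 0.65 SD as about 70% with 60 evaluable and about 62% with 51 evaluable (if drop-outs are not replaced), and the difference detectable with 80% power as 0.74 to 0.80 SD.
3. Say whether drop-outs are replaced, and reconcile the answer with the sixty randomisation numbers in Allocation concealment mechanism.
4. If 80% is claimed for the covariance analysis, give the assumed baseline/week-12 correlation, say whether the SD is that of HbA1c or of its change, and show the power with and without 15% loss.

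The cost is one paragraph and a less favourable stated power, with no extra patients. Keeping 80% for the unadjusted test with unreplaced losses would instead need about 92 randomised, 32 more than planned. Trial status reports 44 recruited and recruitment still open, so the restatement can be made before the analysis.

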### Patient and public involvement

Patients in this trial will not be involved in the design, recruitment, or conduction of the study. After the measure of the samples, the patients will be informed of the results of indicator data in the form of report. The doctor in charge of the patient will be also informed of the results to optimize treatment and the rehabilitation scheme.

### Adherence to study medication

Strategies to improve adherence to intervention protocols include:

(1) Providing professional lifestyle guidance, 2 weeks of TCM treatment, and laboratory index containing liver function, kidney function, HbA1c, fasting blood glucose, postprandial blood glucose, and gut microbiota for free. The outcomes of HbA1c, fasting blood glucose, and postprandial blood glucose are instantly available

(2) Subsidizing the cost of patients’ travel to the hospital for visits

(3) Adding the patient’s network contact address, communicating and solving the patients’ problems at any time, requiring the patient to monitor blood glucose at home regularly and upload blood glucose data, continuing to conduct diabetes education

(4) Checking the number of medicine bags left by the patients at each return visit, as well as confirming the situation of medication

### Quality control and data collection

In order to maintain the high quality of the trial and ensure compliance with the protocol, all researchers and drug administrators participating in the study will receive rigorous training in accordance with the standardized operating procedure (SOP) manual. Researchers should accurately and clearly record patients’ information in accordance with the requirements of the CRF. The correction of error and its time will be marked. The recruited patients will be trained on how to collect stool samples canonically. The stool samples are collected from uncontaminated feces in the middle of the patient’s bowels. A sample collection box (made by Personalbio corporation) will be provided to the patients in advance. The patients will be informed that defecation should be done in the visiting morning as far as possible. The sampling volume is approximately 1/3–1/2 of the collection tube in the box and then to be separated into the 5-ml cryopreservation tubes by the researchers. Within half an hour, the samples will be transferred to the clinical biobank of Dongzhimen Hospital and stored in a refrigerator at −80 °C until testing. During the collection process, the samples are allowed to be temporarily stored at room temperature for no more than 4 h and temporarily stored in −20 °C refrigerator for no more than 24 h. All the data obtained from the research medical record will be uploaded to the digital database in the hospital. Eventually, all completed data will be uploaded to the Chinese Clinical Trial Management Public Platform (http://www.medresman.org.cn/).

### Data monitoring and auditing

The original data should be uploaded and transferred to the electronic case report form (e-CRF). Two administrators should perform 2 separate inputs and proofreading to ensure the accuracy of the data. The quality of the data will be managed through the Dongzhimen Hospital Data Monitoring Committee (DMC), where managers regularly check data sheets for omissions and errors to monitor the integrity of test data. They will also confirm that all associated documents like case report forms, medical charts, and initial hospital admission reports are up to date and monitor the audit trail of the digital database. From the first data entry, as well as each change, deletion, or increase, to the final entry, every digital footprint must be retained in the database system. The audit trail which includes change date, person, reason, and value should be consistent with the original data and open to the auditing of DMC. The DMC consists of endocrinology clinical experts, methodology experts, and biostatisticians, which are independent of the sponsor and have no conflict of interest with the research team. Original CRFs will be reserved at the research center in Dongzhimen hospital for 5 years for reference by researchers after completion of the study. Digital data will be accessed through the search of public title in the Clinical Trial Management Public Platform or the email communication with the first author.

### Statistical analysis

SPSS 20.0 software was used for the statistical analysis of data. Measurement data were described as mean (M) ± standard deviation (SD). Normality of continuous data was evaluated using the Kolmogorov–Smirnov test and Q–Q plot. If the paired samples were in accordance with normal distribution, the *t*-test of the paired samples was used for pairwise comparison. If not, the nonparametric test was adopted. If the two independent samples were in accordance with the normal distribution and homogeneity test of variances, the *t*-test of the independent sample was used. The *t*'-test was used when the variance was not in uniform and the nonparametric test was adopted when the samples were not in accordance with normal distribution. The covariance analysis will be performed regardless of the comparability in the baseline of Hba1c values of the two groups before treatment. Enumeration data like gender and medical history was described statistically by frequency. The chi-square test and Wilcoxon rank sum test were used to determine whether there was comparability between the two groups. All statistical tests are bilateral, and a *P* value ≤ 0.05 would be considered statistically significant.

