### Intervention

Patients in both groups are given the same diabetes education and lifestyle intervention. After basic blood glucose control, the fasting blood glucose is stable at less than 7 mmol/L and postprandial blood glucose is stable at less than 10 mmol/L. In this process, metformin, GSDI (α-glucosidase inhibitor), DPP-4 (dipeptidyl peptidase 4) inhibitor, and GLP-1 (glucagon-like peptide-1) analogue are avoided. Insulin and insulin secretion promoters are allowed. On the basis of standard treatment, the experimental group is given a TCM granule packet. Each packet contains 11 g RG formula, which includes 10 g Coptis root and 1 g ginseng. Patients will take RG formula at least for 3 months, once daily, 11 g each time. The control group is given the same amount of Chinese medicine simulation agent which is taken by the same way. The simulation agent contains dextrin and condiment, which looks and tastes exactly like the RG formula. The course of intervention is 12 weeks, and medicine is given every 4 weeks. Serum and stool samples are collected at baseline and at week 12 for relevant indicators. During the trial, the subjects are forbidden to use other TCM drugs (including proprietary Chinese medicine, TCM injections, etc.). For patients that have other chronic and/or complicated diseases that require long-term control/lifetime medication that does not contradict with inclusion criteria, thus, they can be exempted from medicinal limitation; however, this information should be recorded in detail in the case report form (CRF). Follow-up observation is continued after 12 weeks of administration to determine the subsequent effects of the drug. Dongzhimen Hospital affiliated to Beijing University of Chinese Medicine has insurance to cover for non-negligent harm associated with the protocol. This will include cover for additional health care, compensation, or damages whether awarded voluntarily by the sponsor or by claims pursued through the courts. Should this study provide evidence of the effectiveness of RG formula in controlling blood glucose and relieving discomfort, it will be recommended for the patients to continue taking the medicine with a half or less dose as the dietary supplements. The detailed component of this formula will be informed to subjects and these two traditional herbs are common and available in most pharmacies as over the counter. If the subjects are prone to receive the conventional medicine, the consultation services on the online platform will be provided up to 3 months to help patients to develop a personalized glycemic schedule. This study has been approved by the Ethics Committee of Dongzhimen Hospital.

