
### Outcome measures

The physical condition of patients should be recorded at baseline, week 4, week 8, and week 12.

At the start of the trial, patient’s general information including name, gender, age, education, marriage condition, BMI, etc., will be collected. The complications of diabetes such as diabetic retinopathy, diabetic nephropathy, diabetic peripheral neuropathy, and diabetic peripheral vascular disease should be noted. Other diseases and their corresponding treatment, symptoms, tongue and pulse condition of TCM should also be collected. At week 4 and week 8, two follow-up visits are conducted to collect TCM-related indicators such as symptoms, tongue signs, pulse signs, and symptom diagnosis. At week 0 and week 12, fecal samples and blood samples are collected for quantitative determination of gut microbiota, serum biochemical indicators, and inflammatory indicators.

Stool sample measuring is based on the 16S rRNA sequencing technology of microbiome. It will detect qualified environmental microbial DNA extraction and make the PCR amplification for the general area in V3-V4 primer in DNA base sequence of the designated areas. After a large number of replicated increments, the result will be compared to the existing databank. When the sample passes the inspection, DNA data will be uploaded to Illumina Hiseq 2500 high-throughput sequencing platform for OTU annotation and relative abundance analysis, so as to calculate the species abundance of all samples at phylum, class, order, family, and genus levels. On the basis of these results, the clustering of species abundance, association analysis of common specific OTU, and inter-group differential species analysis will be completed.

Measures of blood samples are divided into biochemical index and inflammation index. As for biochemical index, FBG and PBG are measured by hexokinase method, HbA1c by glycosylated hemoglobin automatic analyzer using the ion-exchange HPLC method, insulin and C peptide by the chemiluminescence method, urea by the colorimetric method, creatinine values by the sarcosine oxidase method, and ALT and AST by the rate method. As for inflammatory indicators, IL-6, TNF-α, and CRP are determined by professional operators using relevant detection kits and enzyme-labeled analyzer (Infinite F50).

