#### Secondary outcomes

The secondary outcomes are mean changes in FBG, PBG, FIL, C-P, IRI, inflammatory factors, and species abundance of gut microbiota. FBG, PBG, FIL, and C-P will be measured to further assess the status of insulin resistance. PBG is obtained by rapid detection of fingertip blood. FBG, FIL, and C-P are obtained by venous blood sample which will be collected after an overnight by a trained medical officer/investigator and transported to a standard laboratory for analysis. Laboratory technicians are blinded to the study participants. The insulin resistance index of the homeostasis model is based on the formula developed by Matthews [33]. The inflammatory factors include interleukin-6 (IL-6), tumor necrosis factor α (TNF-α), and C-reactive protein (CRP). The species abundance of gut microbiota will be based on the second-generation high-throughput sequencing technology.

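### Covariance analysis is named only for HbA1c; as written, the continuous secondary outcomes are compared as changes without a baseline covariate, which gives up precision that would cost nothing to recover

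*Protocol article*

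**What the plan says.** The Statistical analysis section sets general rules for continuous data. For two groups, the rule begins "If the two independent samples were in accordance with the normal distribution and homogeneity test of variances" and leads to an independent-samples t-test. An unequal-variance version is used if the variances differ, and a nonparametric test if the data are not normal. None of these carries a covariate. One further sentence adds a baseline-adjusted analysis: "The covariance analysis will be performed regardless of the comparability in the baseline of Hba1c values of the two groups before treatment". HbA1c is the only variable it mentions. The sentence states neither the dependent variable nor the covariate.

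The Secondary outcomes section says "The secondary outcomes are mean changes in FBG, PBG, FIL, C-P, IRI, inflammatory factors, and species abundance of gut microbiota".

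Baselines are scheduled. The Intervention section states "Serum and stool samples are collected at baseline and at week 12 for relevant indicators", and Outcome measures repeats it: "At week 0 and week 12, fecal samples and blood samples are collected for quantitative determination of gut microbiota, serum biochemical indicators". Table 1 marks FBG, PBG, fasting insulin, C-peptide and inflammatory factors at both baseline and medication week 12. IRI is a homeostasis-model index, so its components are in hand at both times.

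**The concern.** For HbA1c the plan adopts a sound principle: adjust for baseline whether or not the groups happen to look alike. The same reasoning applies to every other continuous outcome with a measured baseline, yet the tests stated for those outcomes have no covariate.

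A change score does use the baseline, but with a slope fixed at 1. If the true regression slope of the week-12 value on baseline is below 1, subtraction over-corrects and leaves baseline noise in the comparison. Covariance analysis estimates the slope from the data instead.

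What is at stake is the width of the intervals, and hence the power, for the secondary glycaemic, insulin and inflammatory outcomes in a trial of 30 per arm. The primary HbA1c comparison is not affected.

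**Working it through.** **Inputs from the article.** 30 per arm, 1:1; two-sided tests ("All statistical tests are bilateral") at 0.05 ("value ≤ 0.05 would be considered statistically significant"); drop-out 15%, leaving 30 × 0.85 = 25.5 per arm. The only planning effect is for the primary outcome: "The sample size was calculated to have 80% power to detect a moderate 0.65-SD difference in HbA1c". No power is claimed for any secondary outcome, so 0.65 SD serves below only as an illustration. (With those planning inputs, 30 per arm gives 70% two-sided power, not 80%. That is a separate matter and this point does not rest on it.)

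**Assumed.** The baseline to week-12 correlation ρ is not given; I take 0.3, 0.5 and 0.7.

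**Variance ratio.** Take equal baseline and week-12 variances, scaled to 1.
- Change score: variance 2(1−ρ).
- Covariance analysis: variance 1−ρ² = (1−ρ)(1+ρ).
- Ratio: (1+ρ)/2.

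| ρ | Ratio | Change-score trial of equal precision (30 ÷ ratio) |
|---|---|---|
| 0.3 | 0.65 | about 46 per arm |
| 0.5 | 0.75 | 40 per arm |
| 0.7 | 0.85 | about 35 per arm |

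At ρ = 0.8 the ratio is 0.90. Estimating the slope costs one residual degree of freedom, about 2% of variance at this size (1 + 1/56 = 1.018 for 60 patients). The powers below use the reduced degrees of freedom but not that 2%; including it lowers the covariance-analysis figures by about one point or less.

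**Illustrative power** (noncentral t, two-sided 5%; covariance-analysis results in the order ρ = 0.3, 0.5, 0.7):
- 0.65 in SDs of the change, 30 per arm: change score 70%; covariance analysis 87%, 81%, 77%.
- The same at 25.5 per arm: change score 62%; covariance analysis 80%, 75%, 69%.
- 0.65 in SDs of the raw value, 30 per arm: change score 55%, 70%, 89%; covariance analysis 74%, 81%, 93%.

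**Effect of the entry limits on FBG and PBG.** The Inclusion criteria require FBG stable below 7 and PBG stable below 10 mmol/L. Write b for the regression slope, V for the baseline variance and R for the residual variance. The change-score variance is R + (1−b)²V and the covariance-analysis variance is R. Under a linear model, selecting on baseline shrinks V but leaves b and R alone, so the excess term shrinks. The article gives no SDs, so this is an illustration with b = 0.5 and R = 0.75:
- V = 1: 0.75 ÷ (0.75 + 0.25) = 0.75; power 70% to about 81–82%, a gain of about 12 points.
- V = 0.5: 0.75 ÷ 0.875 = 0.86; 70% to 76%, about 7 points.
- V = 0.25: 0.75 ÷ 0.8125 = 0.92; 70% to 73%, about 3 points.

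These steps use 0.65 in SDs of the change at 30 per arm.

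**The case against.** The strongest reply is that the restriction to HbA1c is inferred from silence. The covariance sentence does not say that it excludes other outcomes, and a condensed article may leave endpoint-level models to a separate SAP. Part of this stands: restriction to HbA1c is the natural reading, not an explicit one. But the article does not leave the secondary comparison open. It states tests for continuous data, and they are less efficient than the method it names for HbA1c. If wider use was intended, the same edit settles it.

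Four further limits stand.
- A change score is not free of baseline adjustment; it adjusts with a fixed slope.
- The (1+ρ)/2 ratio needs equal variances. The entry limits make that doubtful for FBG and PBG, where the gain is probably smaller. A low correlation caused by a narrowed baseline range does not bring the large gain that the ratio would suggest.
- The powers assume normal data. Insulin, IRI, CRP, IL-6 and TNF-α are likely to be skewed, and the plan sends non-normal data to a nonparametric test, which these powers do not describe.
- HbA1c carries the main efficacy claim and already has covariance analysis named.

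A reader might infer that the secondary results would be biased toward the arm that starts higher. The documents do not support that: allocation is randomised, so a comparison of changes is right on average. A chance baseline difference of one standard error, √(2/30) = 0.26 SD, would shift the change contrast by 0.13 SD relative to the adjusted one at ρ = 0.5. That shift arises from the same slope error that produces the variance loss; it is not an additional harm.

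**Conclusion.** The point holds as one of efficiency. As written, the continuous secondary outcomes are compared without a baseline covariate although the covariate is collected, and the plan gives up precision that it could have at the cost of one degree of freedom. There is no bias and no effect on the primary analysis.

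With equal variances and an assumed ρ of 0.3 to 0.7, the change score carries 18% to 54% more variance than covariance analysis (1/0.85 to 1/0.65). Illustrative power gains at 30 per arm run from 4 to 18 points across the two readings of 0.65 SD, with about 12 at ρ = 0.5. For FBG and PBG the gain is probably less, falling to about 7 or 3 points in the illustration if selection halves or quarters the baseline variance. All of this rests on assumed correlations and variances, because the article gives none. The direction does not depend on them: apart from that one degree of freedom, covariance analysis is no less precise.

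A reader might also conclude that the article rules out adjustment for the secondary outcomes. It does not; it names adjustment only in connection with HbA1c.

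**What to change.** In Statistical analysis, extend the covariance analysis to each continuous secondary outcome (FBG, PBG, fasting insulin, C-peptide, IRI, IL-6, TNF-α, CRP). Model the week-12 value on treatment group and that outcome's own baseline value. Report the adjusted group difference with its 95% CI, and name this as the between-group analysis. Where a marker is clearly skewed, transform it (for example by logs) before fitting. A rank test may stay as a sensitivity analysis.

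The cost is a few sentences of wording and some extra software output. No further patients, visits or samples are needed. The article reports recruitment as still open, with 44 patients entered, and describes a formal amendment route, so on that status the change could be made before unblinding.
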